**Methods/design:**

The RETURN-study prospectively assesses and surveys 200 patients with mental disorders in a cluster randomized intervention study, i.e. treatment teams and patients from intervention wards receive a return-to-work (RTW) intervention. Patients in control wards obtain treatment as usual (TAU). Pairs of comparable wards (similar patient population, similar staff density) have been identified and then randomized for control and intervention (*n* = 14 for each condition). On intervention wards return-to-work experts (RTW experts) who focus treatment on the workplace-related needs of patients with mental illnesses have been established. These RTW experts ensure the use of available resources within the framework of work-related discharge management and should lead to a more successful return to the workplace.

The days at work in the year after release will be evaluated in a mixed methods approach as well as the return rate in the year after release, disability days in the year after return, relapse rate after 12 months, cost-benefit ratio of the intervention, analysis of the predictors / barriers for a successful return to the workplace (e.g. psychopathology, cognition, stigma, social-psychiatric support, company support, etc.), possibilities to implement the concept of RTW experts in standard psychiatric care (TAU - treatment as usual), the impact of the RTW experts’ approach on the treatment process in standard psychiatric care.

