### Setting and participants

The study will be implemented on *n* = 28 acute wards (=clusters) in seven psychiatric hospitals in the greater Munich area. Eligibility criteria for the wards to be included are: acute psychiatric ward in one of the participating hospitals, patients with psychiatric disorders are commonly treated on these wards.

All patients treated on these wards and on admission to the ward, each patient fulfilling the inclusion criteria will be consecutively offered participation in the trial.

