#### Inclusion criteria

· Age 18–60 years.

· Diagnosis of a mental illness [ICD-10 Chapter F2–4, F6 (we assume that the majority of patients with existing employment relationships suffer from an affective disease [14]).

· In a contractual employment relationship, in which they can be reintegrated.

· Psychopathologically capable of reflecting on work in general and on their own work.

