#### Randomization and blinding

We will determine pairs of comparable wards (number of patients, distribution of diagnoses, staff etc.) and then randomize one ward of each pair to the intervention and one ward to the control condition. While the principal investigators will determine the paired wards, the statistical institute of our department (IMedIS) will do the randomization.

Randomization takes place at cluster level (*n* = 14 wards each to the intervention group or control group) to minimize contamination effects [19].

As to the nature of the intervention (implementation of RTW-experts) there will be no blinding.

To avoid selection bias, all patients fulfilling inclusion criteria will be recruited consecutively in the intervention and control group. This process is monitored by the study center and will be reported in form of a CONSORT diagram. There will be special emphasis on documenting how many patients (and for what reasons) did not consent to participate in the trial.

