### Ethics, informed consent procedure and trial registration

The trial has been approved by the local review board (Ethikkommission der Technischen Universität München). The ethics approval covers all study sites under the German Law (Gesundheitsdienst- und Verbraucherschutzgesetz (GDVG) vom 24. Juli 2003; GVBl. S. 452, 752, BayRS 2120–1-U/G; last changed through § 1 Abs. One hundred fourty-five der Verordnung vom 26. März 2019 (GVBl. S. 98)).

All patients will be informed about the general purpose of the trial (i.e. that return to work patterns will be compared between different wards) but not about randomization and about the intervention condition and then asked for their informed consent. The trial has been registered at Deutsches Register Klinischer Studien (DRKS00016037), searchable via its Meta-registry (http://apps.who.int/trialsearch/).

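### Consecutive recruitment is not sufficient to avoid selection bias, because unblinded staff judge patients' eligibility after the ward's allocation is known

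*Protocol article*

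**What the plan says.** The abstract (Methods/design) reports ward allocation as already done: "Pairs of comparable wards (similar patient population, similar staff density) have been identified and then randomized for control and intervention". It also reports the experts as already in place: "On intervention wards return-to-work experts (RTW experts) who focus treatment on the workplace-related needs of patients with mental illnesses have been established". Under Setting and participants, patients enter later: "on admission to the ward, each patient fulfilling the inclusion criteria will be consecutively offered participation in the trial". Under Randomization and blinding, the article states that "Randomization takes place at cluster level" and that "there will be no blinding".

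The protection offered there is: "To avoid selection bias, all patients fulfilling inclusion criteria will be recruited consecutively in the intervention and control group". The study centre monitors this process, a CONSORT diagram reports it, and refusals are documented with reasons.

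One inclusion criterion is: "Psychopathologically capable of reflecting on work in general and on their own work". Another requires an employment contract to which the patient can be reintegrated. Cognitive impairment is an exclusion, and the article gives no threshold for it. Under Ethics, patients learn the general purpose before consent, "but not about randomization and about the intervention condition".

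**The concern.** Randomising wards balances the wards, and in expectation the patients who pass through them. It does not balance patients who are selected after the allocation is known. Here whoever judges eligibility can know the arm, and at least one criterion lies close to the outcome: a patient who can reflect on work is plausibly also one who goes back to it. If the same criterion is applied more strictly, or more generously, on intervention wards, the arms differ at baseline, and the comparison of days in work reads that difference as a treatment effect.

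The article itself describes a reason why the arms might differ in this. RTW experts support ward professionals as well as patients (Intervention and control condition), while the Background says that awareness of work is often too low in usual psychiatric care. Enrolment on an intervention ward also leads to extra help for the patient. On a control ward it brings data collection only.

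**Working it through.** **Order of events.** (1) Wards are paired and randomised, and RTW experts are in place (abstract). (2) A patient is admitted to an already allocated ward (Setting and participants). (3) Eligibility is judged and participation offered, without blinding. (4) The patient consents without being told of randomisation or the intervention (Ethics). (5) T0 takes place shortly after admission (Table 1). The eligibility judgement in step 3 follows a known allocation.

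**What each safeguard reaches.**

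| Safeguard | Order and completeness of offers | Patient's decision to consent | Staff judgement of eligibility |
|---|---|---|---|
| Consecutive recruitment | yes | no | no |
| Intervention not disclosed at consent | no | largely | no |
| Study-centre monitoring, CONSORT diagram, reasons for refusal | reveals | reveals | emphasis is on non-consent |

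The last column has no stated control.

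**The plan's own figures.** A two-sided t-test at 0.05 with 80% power and a standardised effect of 0.5 needs 63.77, so 64 per arm and 128 in total, as stated. The 200 corresponds to 128/200 = 64% retained, or 36% drop-out, inside the stated 30–40%. The concern changes neither figure.

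**Illustrative size.** The article does not say how selective enrolment among eligible patients would be, so the following inputs are assumptions:

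- Selection acts on intervention wards only and favours good prognosis.
- The characteristic that drives selection correlates r = 0.1, 0.2 or 0.3 with days in work.
- A share p of eligible patients is enrolled. For p = 0.5: about 2000 are screened (Sample size calculation). If the Background's figure of about 20% in work applied, 2000 × 0.20 = 400 would be candidates, and 200/400 = 0.5. Age, diagnosis, language and cognition would reduce the 400, so p among truly eligible patients could well be higher. The other value used is p = 0.8.

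The shift in the intervention-arm mean, in SD, is r × φ(z)/p, where φ is the standard normal density at the cut-off z above which a share p lies.

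- p = 0.5: φ(0)/0.5 = 0.3989/0.5 = 0.798
- p = 0.8: φ(−0.842)/0.8 = 0.2800/0.8 = 0.350

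| p | r | Spurious difference (SD) | Share of planned 0.5 | Rejection rate with no true effect, 64 per arm |
|---|---|---|---|---|
| 0.5 | 0.1 | 0.080 | 16% | 7.3% |
| 0.5 | 0.2 | 0.160 | 32% | 14.6% |
| 0.5 | 0.3 | 0.239 | 48% | 26.9% |
| 0.8 | 0.1 | 0.035 | 7% | 5.4% |
| 0.8 | 0.2 | 0.070 | 14% | 6.8% |
| 0.8 | 0.3 | 0.105 | 21% | 9.1% |

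The rejection rates are for a two-sided t-test at 0.05 with independent patients. Clustering is ignored, so they are indicative only.

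**The case against.** The strongest reply is that recruiting after allocation comes with any ward-level intervention that cannot be blinded, and that the article takes several precautions. Patients in both arms are told nothing of the intervention before consent. The study centre watches recruitment, refusals are recorded with reasons, and wards are matched in pairs. An employment contract is largely a matter of fact. Who assesses eligibility, and how the judgement items are made operational, is detail that the full protocol may supply. Most of this stands. It narrows the concern to the eligibility judgement, and it rules out calling the safeguards worthless. It does not rescue the claim that consecutive recruitment avoids selection bias, since that rule takes effect only after eligibility has been decided.

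Three stronger readings are tempting and not supported.

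- **T0 is contaminated, so baseline data cannot show an imbalance.** The article describes the RTW experts' clients as participating patients, which suggests that casework follows enrolment. Table 1 also collects at T0 items that a few days of early contact could not change: prior incapacity days, diagnosis and medical history, education and employment data. What remains is that the article does not state that T0 precedes first RTW contact.
- **The bias favours the intervention.** Staff might equally put forward patients with the greatest need, which would bias towards no effect.
- **RTW experts screen patients.** No text gives them that role. The text does not exclude it either.

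**Conclusion.** The point holds as a limited one. The order of events and the absence of blinding are stated outright, and the only measure that the article offers as avoiding selection bias does not reach the judgement of eligibility. The primary comparison is therefore exposed to identification and recruitment bias. A reader might infer that bias is present, or that the arms will differ by a quarter of an SD, but the article supports neither. The range of about 0.04 to 0.24 SD (7% to 48% of the planned effect) rests wholly on assumed one-sided selection, assumed correlations and an assumed enrolment share. Weak selection would be almost harmless; moderate selection would not. The reason to act is that selection during recruitment cannot be undone afterwards and is cheap to limit beforehand.

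**What to change.** Set one procedure for both arms:

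1. The study centre, which already monitors recruitment, builds the candidate list on every ward from admission data: age, ICD chapter, employment contract.
2. The judgement criteria (reflecting on work, possible reintegration, cognitive impairment) go on a fixed form with reasons, completed by the same professional role and within the same time window after admission on every ward.
3. RTW experts take no part in screening, eligibility or consent.
4. Consent and T0 precede the first RTW-expert contact, and the dates of all three are recorded.
5. During recruitment, numbers screened, judged ineligible (with reason) and consenting are compared by arm within ward pairs.
6. T0 items that early RTW contact cannot alter (prior incapacity days, diagnosis and history, education, employment data) are used to check for imbalance.

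In Randomization and blinding, change the claim from avoiding selection bias to reducing it.

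Cost: a short amendment, a screening form and somewhat more paperwork, with no new staff, and possibly a short delay to first RTW contact. Some bias can remain, because the assessor may still know the arm and equal enrolment rates do not prove equal prognosis.

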### Intervention and control condition

The intervention consists of the implementation of Return to Work experts in the participating acute care units. The RTW experts (social workers, who in the framework of the RETURN study are added to existing resources) support patients and mental health care professionals on the wards in all areas related to the possible return of patients to their workplace. The RTW experts will thereby act as case managers, who usually first clarify the specific needs of the clients (i.e. participating patients who might return to an existing workplace), subsequently communicate these needs to all people involved in the treatment process and initiate and accompany a corresponding treatment path. The services of the RTW expert can be claimed by the patients for up to half a year. In order to guarantee a minimum of intervention, it is planned that the RTW experts meet at least twice – one appointment during the inpatient stay and one after release. A maximum of intervention is not defined. Above all, existing support services (e.g. work therapy, cognitive training, socio-educational counseling, etc.) should be activated for the individual patient. However, if there is a limitation of resources, more specific needs or issues (for example, discussions with the patient’s employer, Integration Services, etc.), the RTW expert can also take personal action and support the patients accordingly. In addition, the RTW expert is to be active at the interface between discharge and reintegration and to assist the patient even after discharge in the activation of occupational and outpatient psychiatric-psychotherapeutic support measures. The RTW experts thus assume the function of a job-related discharge management.

The approach of the RTW experts is guideline-based. The RTW experts will be specifically trained. For this purpose, a guideline and a training program for the RTW experts has been established together with the Advisory Board in the first project phase (Kohl et al. in preparation), and will be evaluated within the framework of the study and then revised if necessary, so that the guideline and RTW expert training can be published at the end of the project.

Staff (and patients) of the control wards will act under “treatment as usual” (TAU) conditions. To avoid contamination bias as far as possible (i.e. staff or patients from control wards getting to know about RETURN), wards were chosen in a way so that there is no overlap in personnel and that there is no regular patient exchange between wards.

### Data collection

The same data at the same time points will be collected in the intervention and control group (Table 1). Data collection will take place at five times during the inpatient stay and after discharge.

**Table 1 Tab1:** Planned data collection

	T0 (shortly after admission to hospital)	T1 (shortly before release from hospital)	T2 (3 months after release)	T3 (6months after release)	T4 (12 months after release)
Patient					
Demographics including information on					
School and vocational training	x				
Employment relationsship	x				
Business, enterprise (industry)	x				
Business, enterprise (size)	x				
Motivation	x	x	x	x	x
Anxiety, confidence	x	x			
Days of incapacity to work	x		x	x	x
COPSOQ	x			x	
COPSOQ (additional information)	x				
Self-stigma of mental illness scale short form – self-concurrence	x	x		x	
Cognitive appraisal of stigma-related stress	x	x		x	
Questions concerning disclosure of the disease at the workplace including					
Questions on the decision-making phase	x	x		x	
Questions on the decision to disclose	x	x		x	
Questions on the attitude towards disclosure	x	x		x	
Decisional Conflict scale	x	x		x	
Cognitive performance level		x			
CSSRI	x	x	x	x	x
Preparation of the return through the hospital		x			
Preparation of the return through the employer		x			
Preparation of the return through the RTW expert (intervention group only)		x		x	
Questions on the existing help network		x		x	x
Content of the employer support				x	
Evaluation of the employer support				x	
Evaluation of the RTW expert support (intervention group only)				x	
EuroQOL - Gesundheitsbarometer	x	x		x	
EQ-5D		x		x	x
Self-efficacy expectation (RTW-SE)		x			
Resilience (RS-13)					x
Patient Health Questionnaire (PHQ-D)		x			
Days at work			x	x	x
Days of incapacity for work			x	x	x
Days of partial return to work			x	x	x
Questions on discrimination at the workplace				x	
Coping				x	
Attending physician					
CGI	x	x			x
GAF	x	x			x
ICD Diagnosis and medical history	x	x			x
HoNOS		x			
Prediction on return to work		x			
RTW expert (intervention group only)					
Type and scope of workplace-related support		x		x	
Evaluation of workplace-related support		x		x	
Prediction on return to work		x			
Quality of relationship		x		x	
Return to work				x	
Questions concerning the use of communication media				x	
Open summary				x	

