### Sample size calculation and statistical analysis

The aim is to obtain a sample of *n* = 28 clusters (i.e. psychiatric acute wards) with a total of 200 patients (8–10 per cluster). For this, about 2000 patients need to be screened (Mernyi et al., 2018).

In order to be able to demonstrate a significant result with a power of 80% assuming a small to medium effect size (0.5), a total sample size of 128 patients is required (two-sided independent samples t-test, α = 0.05). With regard to expected drop-outs (drop-out rate 30–40%), this minimum number of cases is planned to be exceeded by 72 patients. Thus, a total of 200 patients are to be included (100 in each group).

The primary analysis will be a comparison of days in work at T4 between the intervention and control groups. To assess the effect of the intervention on the continuous primary outcome, a random effects linear regression model will be fitted with ward (cluster) as a random effect term and intervention group as a fixed effect. The point estimate for the intervention effect will be reported together with the corresponding 95% confidence interval. A *p*-value < 0.05 will be considered as providing statistical significant evidence of a group difference. A per protocol approach will be taken to the analysis, i.e. patients in intervention clusters will be analyzed in this group, if they had contact with the RTW-expert at least once during their inpatient stay and once after discharge.

Exploratory analyses will be performed to assess the effect of the intervention on the secondary outcome measures. Random effect linear models will be fitted to the continuous secondary outcome measures, analogous to the primary analysis. For binary secondary outcome measures, logistic regression models using GEEs will be fitted.

The health economic analysis is based on the net benefit approach. To analyze the cost-effectiveness of the RWT intervention, the incremental cost-effectiveness ratio (ICER) is determined for gaining a QALY compared to routine treatment. The estimation of ICER stochastic uncertainty is done by nonparametric bootstrapping and the determination of the cost-effectiveness acceptance curve [29].

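### Neither EuroQol measure in Table 1 has both an admission value and a 12-month value, so quality of life at 12 months cannot be adjusted for an admission value on the same scale

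*Protocol article*

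**What the plan says.** Table 1 (Data collection) lists two EuroQol rows. The "EuroQOL - Gesundheitsbarometer" is marked at T0, T1 and T3. The EQ-5D is marked at T1, T3 and T4. The relevant column heads read "T0 (shortly after admission to hospital"), "T1 (shortly before release from hospital") and "T4 (12 months after release").

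The Secondary outcomes section names quality of life, measured by EQ-5D, as a secondary outcome. It does not mention the barometer. The statistical section sets the primary comparison at 12 months: "The primary analysis will be a comparison of days in work at T4 between the intervention and control groups". For secondary outcomes it says "Random effect linear models will be fitted to the continuous secondary outcome measures, analogous to the primary analysis". That primary model contains ward as a random effect and group as a fixed effect. The economic analysis is expressed per QALY: "the incremental cost-effectiveness ratio (ICER) is determined for gaining a QALY compared to routine treatment".

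Under Intervention and control condition, the planned minimum of RTW-expert meetings is "one appointment during the inpatient stay and one after release", and the service is available for up to half a year.

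**The concern.** The trial's horizon is the year after discharge, and quality of life is one of its named secondary outcomes. An analyst would normally want that outcome on one scale both at entry and at 12 months, so that the later comparison can be adjusted for the earlier value. The two EuroQol rows come close but miss each other: one has the admission value and stops at six months, and the other reaches 12 months but starts only at discharge.

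The design gives an admission value more than its usual worth, for three reasons:

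- Whole wards are randomised without blinding, and patients are then recruited on wards whose allocation is known. Consecutive recruitment limits differential enrolment but cannot rule it out.
- The analysis is per protocol. Intervention-ward patients count only if they had one inpatient and one post-discharge RTW contact, and the control wards have no such condition. The secondary models are described as analogous, so the same selection probably applies to them.
- Drop-out of 30–40% is expected.

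Each of these can make the groups compared at T4 differ from admission onward. A covariate measured at admission on the same scale would help to show such a difference and would partly correct for it.

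**Working it through.** The plan gives no figure on this point, so there is none to reproduce. The check is a reading of the schedule, followed by a short calculation under an assumption.

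**Step 1: the marks in Table 1**

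| Measure | T0 | T1 | T2 | T3 | T4 |
|---|---|---|---|---|---|
| EuroQol barometer | x | x | | x | |
| EQ-5D | | x | | x | x |
| GAF (for comparison) | x | x | | | x |

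Both EuroQol rows divide cleanly into five columns, so nothing suggests a conversion error. No other part of the article adds a T4 barometer or a T0 EQ-5D.

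**Step 2: what can be computed**

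- Visits shared by the two EuroQol rows: {T0, T1, T3} ∩ {T1, T3, T4} = {T1, T3}.
- Rows with both T0 and T4: none. No EuroQol change from admission to 12 months exists, and no T4 EuroQol value can be adjusted for a T0 value on its own scale.
- GAF, named in the same list of secondary outcomes for social functioning, does have both T0 and T4.

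**Step 3: can T1 serve as baseline?** The first planned RTW-expert meeting is in the inpatient stay, and T1 is shortly before release. T1 therefore normally follows the start of the intervention, and adjusting for it could remove part of the effect. T0 is the earliest measurement and is probably pre-intervention. The article does not say that T0 precedes the first RTW contact, so this is an inference.

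**Step 4: what a T4 barometer with T0 adjustment would be worth**

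Let r be the correlation between the T0 and T4 barometer values. The document gives no value, so a range is assumed. Residual variance after adjustment, relative to no adjustment, is 1 − r². The equivalent multiple of patients is 1 / (1 − r²).

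| r (assumed) | 1 − r² | 1 / (1 − r²) |
|---|---|---|
| 0.2 | 0.96 | 1.04 |
| 0.3 | 0.91 | 1.10 |
| 0.4 | 0.84 | 1.19 |
| 0.6 | 0.64 | 1.56 |

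These are patient-level figures and ignore clustering by ward.

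**The case against.** The strongest case against runs as follows. The barometer is not a named outcome; EQ-5D is, and it is measured at T4. The planned random-effects model compares groups at 12 months without needing an admission value. Several other instruments (self-stigma, stigma-related stress, the disclosure questions, the Decisional Conflict Scale) have the same T0/T1/T3 pattern, and COPSOQ also stops at T3. A shorter T4 battery may therefore be deliberate. The article does not promise a 12-month barometer result and does not contradict itself. The gain also rests on an assumed correlation between a rating in an acute admission and one more than a year later, which may well be low.

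Most of this stands, and it limits the point. A reader might infer from the table that the trial has no 12-month quality-of-life result, or cannot show whether a difference persists after RTW support ends. The documents do not support either reading, because EQ-5D at T3 and T4 covers both. A reader might also infer that the economic analysis fails. That is not shown either: EQ-5D is measured at three visits, and the article does not set out how QALYs are derived.

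The objection does not remove the gap itself. The T0 barometer value can be used as a covariate for T4 EQ-5D, but that adjustment crosses instruments and gives no change on one scale. The possibility of a deliberately short T4 battery is weaker here than for the stigma and disclosure items, because EuroQol measurement was carried to T4 through EQ-5D and GAF was kept at both ends.

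It is also fair to say that the missing T0 EQ-5D is the larger gap, since EQ-5D is the named outcome and presumably the source of the QALYs. Adding a T4 barometer does not close that gap.

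**Conclusion.** The point holds as a cheap improvement to the schedule, not as an error that threatens a conclusion. The fact is certain: neither EuroQol measure is scheduled at both T0 and T4. The consequence is that no 12-month quality-of-life comparison can be adjusted for an admission value on the same scale. The unadjusted T4 comparison of EQ-5D and its T3-to-T4 course remain available.

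The size is modest and uncertain. At the low end of the assumed correlations the gain in precision is negligible (1.04 times the patients at r = 0.2); at the high end it is useful (1.56 times at r = 0.6). Clustering by ward is not allowed for. The case also rests on T0 preceding the first RTW contact, which is likely but not stated. The primary outcome and the sample size are untouched.

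**What to change.** - In Table 1, mark the EuroQol barometer at T4.
- Analyse the T4 barometer as an exploratory outcome in the planned random-effects model (ward random, group fixed), with the T0 barometer value as covariate.
- Use the T0 barometer value as covariate for T4 EQ-5D as well. This uses data already scheduled and needs no new measurement.
- State whether T0 is completed before the first RTW-expert contact.

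The cost is one additional rating at a contact where EQ-5D is already completed, one cell in Table 1 and one covariate in an exploratory model. No extra visit is needed. The article does not describe what the barometer or the T4 EQ-5D row contains, so the sponsor should first check whether the two already overlap. The change helps only for T4 contacts still to come. It leaves EQ-5D, and QALYs if they are derived from it, without a T0 value of their own.
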